### Training of data collectors

We will recruit data collectors that speak Hausa and Yoruba to administer baseline and follow-up surveys. Since data collectors will be Hausa-speaking, it is quite likely that they will also be familiar with Hausa culture in southwest Nigeria. Even so, they will be trained to interact politely with elders and to dress appropriately to facilitate the building of trust and rapport with participants. Male and female data collectors will work in pairs to respect gender norms in the Hausa community and maintain the security of our research team. Female participants will be interviewed by female data collectors; male participants will be interviewed by male data collectors.

### Data collection and management

Participants will be asked whether they are most comfortable speaking Hausa or Yoruba and the survey will be conducted in their preferred language. Yoruba is the most commonly spoken language in Southwest Nigeria and some Hausa persons may be more comfortable speaking Yoruba. They will be asked to provide informed consent in their language of choice before beginning the baseline survey.

Reponses to survey questions will be entered directly into Research Electronic Data Capture (REDCap) software loaded on electronic tablets [31]. The College of Medicine at the University of Ibadan is a member of the REDCap consortium and is permitted to use this software. The REDCap mobile application can be used for offline data collection, which makes it suitable for use in this study setting where internet connectivity is unstable. The Field Supervisor will ensure that all data collected offline is sent to the REDCap server on a daily basis. Data will be exported from REDCap to Stata version 17 for analyses [32].

Participant’s names, cell phone numbers, and residential addresses will be collected so that we can reach them for a follow-up interview. We will also ask each participant to provide the name and phone number of a family member or friend who can be contacted if the participant cannot be reached for a follow-up interview. In that case, we will ask the friend about the participant’s status (e.g., whether they are ill or have moved away) so that we can minimize loss to follow-up during the study. After the follow-up interview is completed, we will assign each participant a code number and remove all personally identifying contact information from the data. All contact information for family or friends will also be deleted at that point.

### Statistical analyses

We will measure the impact of our intervention by comparing the change in outcomes between baseline and follow up in the intervention site (Ibadan) with the change in outcomes between baseline and follow up in the control site (Akure). Outcomes will be modelled using the following basic equation:

$$Y_{i}=\alpha +\beta C_{i}+{\gamma T}_{i}+\delta (C_{i}*T_{i})$$

This model posits that the outcome for an individual *i* (*Y_i_*) is a function of the city they live in (*C_i_*) and the time point *T_i_* (baseline or follow-up). The coefficient *δ* represents the treatment effect we are interested in. We will use the coefficients obtained from a logistic regression model to estimate the marginal probability of each outcome among the intervention and control samples and subtract these estimates to calculate risk differences.

Demographic covariates measured at baseline may be added to this model to account for any observed differences between intervention and control samples at baseline.

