### Research design

We will measure the impact of our intervention using a controlled, pre-post design. A baseline survey will be conducted in both cities prior to the intervention to measure knowledge and perceptions of child marriage, including the ideal age for marriage among boys and girls, the perceived benefits and harms of marrying early, and knowledge of the minimum age for marriage specified by law. The baseline questionnaire was written in English and will be translated into Hausa and Yoruba, the primary languages spoken among Hausa persons living in Ibadan and Akure.

The radio dramas will be broadcast in Ibadan for a period of three months. Afterward, we will follow up with the same individuals who participated in the baseline survey in both cities and ask them to complete a second interview. The follow-up interview will measure coverage of the intervention, i.e., whether participants heard the radio dramas, and will ask many of the same questions as the baseline interview so that we can measure changes in these outcomes over time.

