### Pre-determined outcomes and sample size calculations

During the process of applying for funding for this research, the authors were required to specify a threshold for demonstrating “proof-of-concept” to the funding agency, Grand Challenges Canada (GCC) [29]. (Under GCC’s funding model, projects that demonstrate proof-of-concept may be eligible for expansion and longer-term funding). The authors and the funding agency agreed in advance on the outcomes and the minimum relative change in those outcomes that would be considered sufficient evidence to demonstrate that the intervention seems promising, i.e., demonstrates proof-of-concept:

A 10% increase in the proportion of participants who can identify at least one harmful consequence of child marriage for girls’ health, education, and/or economic opportunitiesA 20% increase in the proportion of participants who know that marriage before the age of 18 is illegal in Oyo State, Nigeria (where Ibadan is located)A 10% reduction in the proportion of participants who believe that the ideal age for girls to marry is younger than 18A 10% reduction in the proportion of participants who would support the marriage of girls in their families before the age of 18.

These pre-determined outcomes and the specified minimum change in those outcomes guided our sample size calculations. We want to be sure that we have sufficient statistical power to detect the effect sizes described above with a high degree of precision and, ideally, to detect even smaller effects. Assuming that 20% of persons surveyed at baseline already have the outcome of interest, we estimate that with a sample of 1600 persons, 50% of whom will be assigned to the treatment group (i.e., living in Ibadan), we can detect a minimum change of five percentage points in each outcome with 80% power at an alpha level of 0.05 [30].

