### Sampling procedure

Participants will be recruited through a multi-stage cluster sampling approach. In the first stage, enumeration areas (called settlements) within known Hausa neighbourhoods (wards) of Ibadan and Akure will be randomly selected from existing lists developed by health care centres in those wards. In the second stage, houses within selected enumeration areas will be randomly selected using lists obtained from the Nigerian National Population Commission (NPC). Multiple households often reside within the same residential building in these cities. Every household in a selected building that includes at least one eligible participant will be invited to participate. If households include more than one eligible participant, one individual will be randomly selected. If buildings selected from the NPC lists are abandoned or not in residential use at the time of the survey, new buildings will be randomly selected to replace them. Using this sampling approach, we will randomly select a total of 1600 persons to participate: 800 in Ibadan and 800 in Akure.

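### The stated logistic model makes no provision for repeat interviews of the same persons or for cluster sampling, so ordinary standard errors for the treatment effect would be invalid

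*Protocol article*

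**What the plan says.** The Statistical analyses section of the Protocol article announces "Outcomes will be modelled using the following basic equation" and prints an intercept, a city term, a time term and their product, indexed by person. It continues: "We will use the coefficients obtained from a logistic regression model to estimate the marginal probability of each outcome", and these probabilities are then subtracted to give risk differences. Baseline demographic covariates may be added. No variance estimator is named there or elsewhere in the article.

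Two other sections fix a design with dependent observations:

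- Research design: after the broadcasts, "we will follow up with the same individuals who participated in the baseline survey in both cities". Each retained person therefore contributes two rows.
- Sampling procedure: "Participants will be recruited through a multi-stage cluster sampling approach". Settlements are drawn, then buildings, and "Every household in a selected building that includes at least one eligible participant will be invited to participate", with one person taken per household. The target is "800 in Ibadan and 800 in Akure".

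The sample size section begins "Assuming that 20% of persons surveyed at baseline already have the outcome of interest" and gives five percentage points as the detectable change at 80% power and alpha 0.05. It states no within-person correlation, intracluster correlation or design effect. On data handling, the article says that after follow-up "we will assign each participant a code number and remove all personally identifying contact information from the data".

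**The concern.** The printed model describes the mean outcome in four cells (two cities, two times). Nothing printed with it reflects that the two rows of one person are correlated, or that people in one building or settlement may answer, and change, alike. An ordinary logistic fit treats all rows as independent.

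The two dependencies push in opposite directions. Positive correlation between a person's two answers makes the true variance of the change smaller than the independent-rows variance. The intervals are then too wide, and the precision that re-interviewing was meant to buy is lost. Shared change within a settlement makes the true variance larger, so the intervals are too narrow and false positives rise. Settlement differences that stay constant over time cancel in the change, so what matters is whether change itself clusters. The article gives a reason to expect that: its Intervention section describes radio listening as something adults often do together, so neighbours would share exposure.

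At stake are the confidence intervals and p-values for every survey outcome analysed with this model.

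**Working it through.** **Inputs.** From the article: 800 persons per city, baseline proportion 0.20, a change of 5 points, alpha 0.05. Assumed, because the article gives no values: within-person correlation rho 0.2 to 0.6, persons per settlement m 10 to 40, and intracluster correlation of the change (ICC) 0 to 0.05. Follow-up is taken as complete.

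**The plan's own figure.** A two-sided comparison of two proportions, 800 per city at one time point:

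- 20% v 25%: null SE = sqrt(2 × 0.225 × 0.775/800) = 2.088 points; alternative SE = sqrt((0.16 + 0.1875)/800) = 2.084 points. Power = Φ((5 − 1.96 × 2.088)/2.084) = 66.8%.
- 20% v 15%: power is 75.0% by the same formula.

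So the stated 80% does not reproduce this way. It returns under choices the article does not state: a one-sided test with constant variance 0.16 (detectable change 4.97 points), or a paired difference-in-differences with rho about 0.58 to 0.62 and no clustering. The stated power therefore does not show which variance is intended.

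**Ordinary standard error.** On the risk-difference scale, with all four cells at 20%: sqrt(4 × 0.16/800) = 2.83 points.

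**True standard error.** Pairing multiplies the variance by (1 − rho). Clustering of change multiplies it by 1 + (m − 1) × ICC. Hence

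true SE / ordinary SE = sqrt[(1 − rho) × (1 + (m − 1) × ICC)],

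and the actual error rate of a nominal two-sided 5% test is 2 × [1 − Φ(1.96 / ratio)].

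| rho | m | ICC of change | true/ordinary SE | actual error rate |
|---|---|---|---|---|
| 0.2 | any | 0 | 0.894 | 2.8% |
| 0.4 | any | 0 | 0.775 | 1.1% |
| 0.6 | any | 0 | 0.632 | 0.2% |
| 0.6 | 10 | 0.01 | 0.660 | 0.3% |
| 0.4 | 40 | 0.02 | 1.033 | 5.8% |
| 0.4 | 40 | 0.05 | 1.330 | 14.1% |
| 0.2 | 40 | 0.05 | 1.536 | 20.2% |

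In the first three rows the ordinary SE is too large by 1/0.894 = 1.12, 1/0.775 = 1.29 and 1/0.632 = 1.58. The two errors cancel exactly only when (m − 1) × ICC = rho/(1 − rho), which no part of the design ensures.

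**Cost in power when only pairing operates.** Take 20% to 25% in Ibadan against a flat 20% in Akure. The ordinary SE is sqrt((3 × 0.16 + 0.1875)/800) = 2.889 points. At rho 0.4 the true SE is 2.239: power is 61% with the correct SE, but Φ((5 − 1.96 × 2.889)/2.239) = 38% with the ordinary one. At rho 0.6 (true SE 1.829) the figures are 78% and 36%.

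**Simulation under no effect.** The printed model was fitted to simulated data.

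- 40 settlements of 20 persons per city, 600 runs per scenario. Ordinary standard errors rejected 1.0% of the time with person correlation only, 1.5% with settlement effects constant over time, 5.7% with a modest settlement-by-time effect, and 12% to 16% with larger ones. Settlement-clustered errors gave 4.3% to 6.2%.
- 20 settlements of 40 persons per city, 400 runs. Ordinary errors rejected 0% (rho 0.6, no clustering) and 13% (rho 0.3, settlement-by-time SD of 10 points). Settlement-clustered errors gave 4.5% to 6.5%.

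Monte Carlo error around 5% is sqrt(0.05 × 0.95/600) = 0.9 points and sqrt(0.05 × 0.95/400) = 1.1 points, so the clustered results are compatible with the nominal level.

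**The case against.** The strongest defence is that the article is silent on variance and nowhere declares that rows are independent. It calls the equation basic. A mean model in city, time and their product needs no person or settlement term to be valid: with settlement-clustered standard errors, the same equation is a correct population-averaged model. A fuller analysis plan, not shown, may say so. This stands as far as it goes. It rules out saying that the mean model is wrong, or that every standard error and p-value will be. The error depends on how the model is fitted, and the two effects can nearly offset (5.8% in the table). What remains is that the article prints a specific model beside a panel design with cluster sampling, and nothing in it connects the two.

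A reader might infer more, which the article does not support:

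- *That the effect estimates are distorted.* The variance choice leaves delta and the risk difference unchanged. The agreed proof-of-concept thresholds are relative changes in proportions, with no significance condition.
- *That the model cuts power from 80% to about 40%.* With independent rows, difference-in-differences power for 20% to 25% is 41% even at rho 0, where ignoring pairing costs nothing. Most of the gap from 80% belongs to the sample size section.
- *That attrition will enter delta.* The article does not say that all baseline respondents will be compared with only those retained, and it describes tracing to limit loss.
- *That cluster identifiers will be lost.* Only identifying contact information is to be removed. A settlement code is a sampling variable, and nothing says it will be deleted.

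**Conclusion.** The point holds as a mismatch between stated design and stated analysis. If the model is fitted as written with ordinary standard errors, inference for delta and the risk differences is invalid. Over rho 0.2 to 0.6, m 10 to 40 and ICC of change 0 to 0.05, the actual error rate of a nominal 5% test runs from about 0.2% to about 20%, against roughly 4% to 6.5% with settlement-clustered standard errors. These ranges are assumptions, and the article cannot narrow them. The 20% end needs large settlements and a low within-person correlation. Low correlation is the less likely case when the same people answer identically worded questions. The conclusion does not depend on which end is nearer: an interval that is right only when two unknown errors cancel is not a sound plan.

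**What to change.** Keep the equation and add a sentence to Statistical analyses along these lines: *Inference for delta and for the risk differences will use standard errors clustered on settlement, the first-stage sampling unit, within which buildings, households and repeat interviews are nested; if there are fewer than about 30 to 40 settlements, a wild or cluster bootstrap will be used.* The risk-difference intervals should come from the same clustered fit. Any restated power figure should use the matching variance.

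In Data collection and management, state that an anonymous settlement code and building code stay in the de-identified data when contact details are removed. This protects the sponsor's own analysis and any reuse of the public dataset.

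The cost is a sentence or two, one option in Stata and two retained codes. There is a downside: intervals may widen if settlements change together. Clustering on settlement also does not remove the limitation of a single city per arm, which no choice of standard error within city can repair.

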### Status and timeline of the study

This study has received ethical approval from the University of Ibadan College of Medicine Institutional Review Board and the McGill Faculty of Medicine and Health Sciences Research Ethics Board. This protocol was initially submitted to PLOS ONE in August 2022 and peer reviews were received in February 2023. Recruitment of participants for the baseline survey began in February 2023. The radio dramas are currently being developed and we anticipate they will be aired beginning in April 2023.

Anonymized, individual-level data will be made publicly available through the Open Science Foundation (OSF) no later than two years following conclusion of the follow-up interview.

## Discussion

Innovative interventions targeting child marriage that are cost-effective and rapidly scalable are needed in Nigeria. Legislation against child marriage has thus far failed to curb the practice and it remains common, particularly among Hausa girls. We will evaluate whether targeted, culturally appropriate radio programming can change knowledge of and support for child marriage among Hausa adults living in Ibadan, Nigeria. This intervention is innovative for several reasons. First, the ability of stand-alone media campaigns to inform and change attitudes toward child marriage has never been evaluated using an experimental or quasi-experimental research design, according to three systematic reviews of such interventions [9–11]. Second, the intervention is readily scalable and cost-effective compared to other promising interventions such as cash transfer programs or modifying national or regional education policies (e.g., eliminating tuition fees). Third, the intervention targets adults who are influential in making marriage decisions for children in their families. Prior interventions have sometimes targeted girls themselves, an approach that may have limited impact if girls’ agency to make decisions about their marriages is restricted.

### Limitations

Funding for this study has been provided for a one-year period, which severely limits the timeframe for this intervention. The radio dramas will air for a period of three months. Earlier educational interventions that had a positive effect on gender equitable attitudes ran for more than two years [12, 13]. The limited timeframe to evaluate the intervention means that we cannot estimate its effect on actual behaviours like the incidence of child marriage. Instead, we will measure support for those behaviours, which may be a precursor to them. Our intervention may not be able to bring about a measurable change in attitudes over such a short period. However, we have powered our study to be able to detect relatively small effects, which would still be interesting for two reasons. First, if our short-term intervention results in small changes in the outcomes of interest, it is plausible that a longer-term intervention would result in stronger effects. Second, even a small effect from such a short-term and cost-effective intervention may be worth fielding more broadly among populations with high rates of child marriage.
